
Motivation level with regard to experimental tasks will be assessed using a Multidimensional Intrinsic Motivation Inventory (IMI). The inventory consists of 4 subscales with a total of 22 questions that can be calculated separately;

1.interest and enjoyment (8 questions);2.perceived competence (5 questions), perceived choice (5 item) and pressure and tension (5 item).

The IMI has adequate reliability value, indicated by Cronbach's α coefficient (ICC = 0.85).^[36]^ The score ranges from 1 to 7 (1 indicates “not at all true”; 4 indicates “somewhat true”; 7 indicates “very true”) and a higher total score signifies a higher level of motivation level (high 7.00–4.67; average 4.66–2.34; low 2.33–1.00).

Self-efficacy: The stroke self-efficacy questionnaire (SSEQ), a 13-item self-administered questionnaire which designed specifically for stroke survivors will be used to assess the level of self-efficacy among the study participants. SSEQ consists of 2 self-efficacy domains: activity (items 1–8) and self-management (items 9–13).^[37]^ Participants need to rate their confidence level on a 3-point scale, from 0 which indicates “not at all confident” to 3 which represents “very confident.” The total score of SSEQ will be calculated by summation of each item score. Higher score of SSEQ indicates higher self-efficacy level. SSEQ has good reliability, with Cronbach α coefficient value 0.90 and person separation index (PSI) >0.80 for both activity and self-management domains.^[37]^ The SSEQ was shown to have high test-retest reliability in stroke survivors (ICC = 0.86)^[38]^ and excellent correlation with the Fall Efficacy Scale (*r* = 0.803).^[37]^

Quality of life: Short Form-36 (SF-36) will be used to measure quality of life of the participants. SF-36 contains 8 domains (36 questions) and can be calculated separately which is divided into;

1.physical health component represented by physical functioning (10 questions), role limitation due to physical health (4 questions) and pain (2 questions),2.mental health component represented by social functioning (2 questions), role limitation due to mental problem (3 questions) and emotional wellbeing (5 questions); and3.physical and mental health component represented by general health (5 questions) and energy/fatigue 4 questions).

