### Assessment of outcomes

2.6

The baseline and therapy outcomes at the end of week 12 of interventions and at a follow up at week 12 and 24 of trial completion will be measured by a therapist who is blinded to the group allocation and trained to conduct the standardized tests. To avoid assessment bias, the recorded baseline assessment data will not be accessible to the blinded assessor during the post-trial and follow-up assessments.

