### Sample size

2.7

The required sample size for this study was estimated using GPower software version 3.0.10. This study will use mixed model analysis of variance (ANOVA) to analyze time, group and interaction effects of the interventions. Therefore, F-test (ANOVA repeated measure, within-between interactions) was chosen and inputted into the system. The study power and alpha value was set at 80% and 0.05, respectively. Based on these inputs, a minimum sample of 82 subjects is required, that is, 41 participants in each trial group.

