### Data analysis

2.8

All data will be entered into IBM Statistical Packages for Social Sciences (SPSS) version 25.0. Intention-to-treat (ITT) analysis approach will be used; all the recruited participants will be included in the outcome analysis. Using ITT approach, missing data will be replaced with “last observation carried forward.” Socio-demography and health profile of the participants will be analyzed descriptively and reported as frequencies (percentages) and mean (standard deviation) or median (inter-quartile range). The effects of the interventions will be analyzed using mixed model ANOVA and reported as main time, group and time-group interaction effects for each outcome variable. Level of significance is set as *P* < .05 for all results.

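### The IMI rates motivation towards the trial tasks, yet the plan implies a rating before the trial sessions that serves as the first level of the time-by-group test and can be carried forward as an outcome

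*Protocol article*

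**What the plan says.** **Construct.** Section 2.5 (Outcomes) introduces the measure as follows: "Motivation level with regard to experimental tasks will be assessed using a Multidimensional Intrinsic Motivation Inventory (IMI". Besides interest and enjoyment, its subscales are "perceived competence (5 questions), perceived choice (5 item) and pressure and tension (5 item". No other activity is named as the thing being rated.

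**Timing.** Section 2.6 (Assessment of outcomes) covers all outcomes in one sentence: "The baseline and therapy outcomes at the end of week 12 of interventions and at a follow up at week 12 and 24" after trial completion. The IMI is not exempted.

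**Analysis.** Section 2.8 (Data analysis) applies a mixed model ANOVA, "reported as main time, group and time-group interaction effects for each outcome variable". Section 2.7 (Sample size) uses the same test: "F-test (ANOVA repeated measure, within-between interactions) was chosen and inputted into the system".

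**Missing data.** Under the intention-to-treat approach in section 2.8, "missing data will be replaced with “last observation carried forward". No outcome is exempted.

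**The concern.** Enjoyment of a task, perceived competence at it, and choice or pressure while doing it can be reported only by someone who has done it. The game board was designed for this trial, and the article describes no familiarisation session. A baseline answer is therefore an expectation, or refers to some other activity that may differ between participants. The analysis nevertheless treats it as an earlier measurement of the same quantity.

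Three things are at stake:

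- whether a change in motivation can be interpreted;
- what is entered as the outcome for participants lost before week 12;
- possibly, power.

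Motivation matters here. It is in the study aim, the abstract says the effect of circuit exercise on it has not been reported, and the Discussion presents it as a route by which the game should work.

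**Working it through.** **1. Does the text put the IMI at baseline?** Not in so many words. Section 2.6 lists baseline among the assessment times for outcomes in general, and section 2.8 requires a time factor for each outcome variable. Read together, they make the baseline IMI the first of four time levels.

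**2. The plan's own figure.** Section 2.7 gives 82 participants (41 per arm) and states: "The study power and alpha value was set at 80% and 0.05, respectively". The effect size, number of measurements and correlation are not given, so 82 can be neither confirmed nor refuted. For the within-between interaction, with λ = f²·N·m/(1 − ρ) and degrees of freedom (m − 1) and (N − 2)(m − 1), N = 82 is reached with m = 4, ρ = 0.5, f = 0.13, and also with m = 3, ρ = 0, f = 0.20. The point does not rest on this figure.

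**3. A two-point check.** Let r be the correlation between baseline and week-12 IMI, with equal variances. Then Var(change)/Var(week 12) = 2(1 − r). If the week-12 score is instead adjusted for baseline as a covariate, the ratio is 1 − r². For a comparison with 80% power on week 12 alone, power = Φ(2.80/√ratio − 1.96), ignoring the one degree of freedom that the covariate uses.

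| r | ratio, change | power, change | ratio, covariate | power, covariate |
|---|---|---|---|---|
| 0 | 2.0 | 51% | 1.00 | 80% |
| 0.3 | 1.4 | 66% | 0.91 | 84% |
| 0.5 | 1.0 | 80% | 0.75 | 90% |
| 0.6 | 0.8 | 88% | 0.64 | 94% |

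The change score loses power below r = 0.5 and gains above it. Covariate adjustment is never worse than change, because 1 − r² = (1 − r)(1 + r) ≤ 2(1 − r).

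**4. The test the plan names.** The plan uses a four-time interaction, not a two-point change, so that test was simulated: 4,000 trials per setting, 41 per arm, no missing data. The assumptions, none of them from the article, are SD 1, correlation 0.6 among the three later visits, correlation r between baseline and each later visit, and the same group difference at all three later visits.

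| Difference | r | four-time interaction | week 12 alone | mean of three later visits |
|---|---|---|---|---|
| 0.62 SD | 0 | 59% | 80% | 90% |
| 0.62 SD | 0.3 | 72% | 80% | 90% |
| 0.62 SD | 0.6 | 91% | 79% | 91% |
| 0.50 SD | 0 | 43% | 62% | 75% |
| 0.50 SD | 0.3 | 55% | 61% | 75% |
| 0.50 SD | 0.6 | 73% | 61% | 75% |

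The week-12 column should not depend on r, and its small movement is simulation error; direct calculation gives 80% at 0.62 SD and 62% at 0.50 SD. With no true difference, the interaction test rejected in 6.5%, 5.8% and 4.9% of trials at r = 0, 0.3 and 0.6. The excess at r = 0 comes from non-sphericity. The other tests stayed near 5%.

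**5. Carrying forward.** The first assessment after baseline is at week 12. Anyone lost before it has only a baseline IMI, and that value fills all three later visits. If a fraction d is lost in each arm, unrelated to outcome, these participants contribute an expected group difference of zero. A true difference δ then appears as (1 − d)·δ. The simulation has no missing data and does not cover this.

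**The case against.** The other side has four arguments of substance.

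- **The control tasks may not be new.** The abstract describes the control circuit as what physiotherapists usually run. Section 2.1 recruits from the hospital physiotherapy department's own database, and section 2.2 excludes home physiotherapy and traditional therapy but not hospital physiotherapy. A reader might infer that no participant has done any of the tasks and that the baseline score is meaningless. The article does not support that; only the game board is clearly new. This stands, but it does not rescue the baseline, because the score would refer to different things for different people.
- **The anchoring may be in the full protocol.** An article can leave the wording of a questionnaire to the full document, and a missing anchor alone would be no finding. Here, however, the article itself states the construct, the times, one analysis for every outcome and one missing-data rule, and these do not fit together.
- **The randomised comparison is sound.** Both arms have the same expected baseline, and type I error stays near 5%. A reader might infer that the interaction test is biased or invalid. It is not, and this stands in full.
- **The power loss depends on an assumption.** The 51% and 66% figures belong to a two-point change score at r = 0 and 0.3. The planned test does less badly there, and at r = 0.6 it beats week 12 alone. A general statement that power falls is not supported.

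Carrying forward is also a general feature of the plan. Nor can one say that early dropouts are scored on tasks they never did: someone leaving at week 8 may have attended many sessions. What is specific to the IMI is that the carried rating predates the activity it is meant to rate.

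**Conclusion.** The concern holds in a limited form. As written, a rating made before exposure is treated as an earlier level of motivation towards the trial tasks, and it becomes the outcome for anyone lost before week 12. The time effect and the change score for this outcome therefore cannot be read as change in motivation towards the tasks. This conclusion rests on the text alone, with one inference: that the generic timing and analysis sentences include the IMI.

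The effect on power is conditional. With 0.62 SD at each later visit and 41 per arm, the planned interaction has about 59%, 72% and 91% power at r = 0, 0.3 and 0.6, against 80% for week 12 alone. The effect size and correlations are assumptions. The documents do not support reading this as an invalid test, a certain loss of power, or a baseline without any information. The plan should be changed because the mismatch affects one of the outcomes named in the study aim and is cheap to remove.

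**What to change.** 1. In section 2.8, make the between-arm comparison of the IMI at the end of the intervention (week 12) the motivation analysis, and exempt the IMI from the time-by-group test that starts at baseline.
2. If a baseline IMI is kept, have it refer to one activity common to both arms, such as current exercise or physiotherapy, say so in section 2.5, and use the score only as a covariate.
3. Do not carry a pre-treatment IMI forward as an outcome.
4. Label the IMI at 12 and 24 weeks after completion as recall of the tasks.

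An IMI taken after the first session or two should not serve as the baseline instead. It is post-randomisation and already contains treatment effect, so a test of change from it would miss any immediate effect of the game.

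The cost is a few sentences and, if a baseline IMI is kept, one line of instruction on the questionnaire. The downside is that change from pre-treatment is no longer reported for this outcome. No visit is added and the other outcomes are untouched.

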### Assessment of outcomes

2.6

The baseline and therapy outcomes at the end of week 12 of interventions and at a follow up at week 12 and 24 of trial completion will be measured by a therapist who is blinded to the group allocation and trained to conduct the standardized tests. To avoid assessment bias, the recorded baseline assessment data will not be accessible to the blinded assessor during the post-trial and follow-up assessments.

### Sample size

2.7

The required sample size for this study was estimated using GPower software version 3.0.10. This study will use mixed model analysis of variance (ANOVA) to analyze time, group and interaction effects of the interventions. Therefore, F-test (ANOVA repeated measure, within-between interactions) was chosen and inputted into the system. The study power and alpha value was set at 80% and 0.05, respectively. Based on these inputs, a minimum sample of 82 subjects is required, that is, 41 participants in each trial group.

### Data analysis

2.8

All data will be entered into IBM Statistical Packages for Social Sciences (SPSS) version 25.0. Intention-to-treat (ITT) analysis approach will be used; all the recruited participants will be included in the outcome analysis. Using ITT approach, missing data will be replaced with “last observation carried forward.” Socio-demography and health profile of the participants will be analyzed descriptively and reported as frequencies (percentages) and mean (standard deviation) or median (inter-quartile range). The effects of the interventions will be analyzed using mixed model ANOVA and reported as main time, group and time-group interaction effects for each outcome variable. Level of significance is set as *P* < .05 for all results.

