Circuit exercise has been found to improve stroke survivors’ functions and quality of life.^[10–16]^ However, the conventional form is seen as less enriched and lacking in fun. Training in enriched and fun environment can promote neuroplasticity, in addition to facilitate personalized motivation and cease stress and anxiety among stroke survivors.^[17–20]^ Nonetheless, no studies have incorporate design-for-fun games environment into the existing circuit exercise. Past studies about circuit exercise have also not included motivation and self-efficacy, 2 important determinants for recovery among stroke survivors^[21]^ in their assessment of intervention outcome despite the fact that stroke survivors frequently demonstrate decline in these component and affect their functional independence over time.^[21–26]^ There is a need to review the existing conventional circuit exercise and offer a more enriched environment by adding multisensory stimuli and cueing, limb integration and cognitive stimulation to further increased neuroplasticity potentials such as game-based circuit exercise.^[27]^ Therefore, the purpose of this study is to determine the effectiveness of game-based circuit exercise in comparison to conventional circuit exercise on functional outcome, motivation level, self-efficacy and quality of life among stroke survivors. This study also aims to assess whether the outcomes gained from the 2 interventions could be sustained at week 12 and week 24 post trial.

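### Carrying the last observation forward tilts the durability aim toward a sustained effect, and dilutes the treatment effect when participants leave during training

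*Protocol article*

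**What the plan says.** Section 2.8 (Data analysis) takes an intention-to-treat approach in which "all the recruited participants will be included in the outcome analysis", and then settles how gaps are filled: "Using ITT approach, missing data will be replaced with “last observation carried forward". No other method is named, and the rule is not limited to any visit or outcome. Effects are to be "analyzed using mixed model ANOVA and reported as main time, group and time-group interaction effects for each outcome variable".

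The abstract and section 1 (Introduction) set a second aim, to "assess whether the outcomes gained from the 2 interventions could be sustained at week 12 and week 24 post trial". Section 2.6 (Assessment of outcomes) supplies the visits: after baseline, measurements are taken "at the end of week 12 of interventions and at a follow up at week 12 and 24 of trial completion". That makes four visits.

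Three other statements bear on the point:
- The abstract opens by describing stroke survivors as prone to functional decline.
- Section 2.9 lets participants leave at any time without giving a reason.
- Section 3 (Discussions) suggests that the enjoyment of the game could influence adherence during training.

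**The concern.** The rule makes a different assumption depending on when a participant is lost.

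- **Lost after the end-of-treatment visit.** The end-of-treatment score is copied into both follow-ups. The change since treatment is then zero by construction, which is the result the durability aim is meant to test. A participant lost between the two follow-ups has the change between them set to zero in the same way.
- **Lost during the 12 weeks of exercise.** The baseline score is copied into every later visit, so no gain is recorded.

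A flat course after treatment fits poorly with the article's own premise of functional decline. The durability result could therefore look better than the data justify, and the treatment effect could look smaller. If the arms lose participants at different rates, the comparison between them can shift as well. Because the article states the choice outright, an analysis plan that follows it would inherit the problem.

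**Working it through.** **The plan's own figure.** Section 2.7 gives 82 participants (41 per arm) from a repeated-measures interaction F-test; "The study power and alpha value was set at 80% and 0.05, respectively". The effect size and the correlation between visits are not printed, so 82 can only be solved backwards. With four visits it corresponds to f = 0.13 at correlation 0.5 (0.10 to 0.18 for correlations from 0.7 down to 0). This is no evidence of error and does not affect what follows.

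**Inputs.** The rule, the visits, the arm size and the aims come from the article. Loss rates, gains, SD and correlation are assumptions.

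**1. Durability.** Let r be the fraction of the gain truly kept at the last follow-up. Let p be the share of those seen at end of treatment who are then lost. Suppose the lost would have followed the same course as the others.

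Fraction shown as kept = (1 − p) × r + p × 1. Decline shown = (1 − p) × true decline.

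| True r | p = 10% | p = 20% | p = 30% |
|---|---|---|---|
| 75% | 77.5% | 80% | 82.5% |
| 50% | 55% | 60% | 65% |
| 0% | 10% | 20% | 30% |

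Equal loss in the two arms does not remove this.

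**2. Dilution.** With a share q = 20% lost before the end-of-treatment visit in both arms, a true difference of 0.50 SD becomes 0.50 × (1 − 0.20) = 0.40 SD, if those lost would have gained like the others.

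For power, take a generic two-group comparison designed for 80%, with standardised signal 1.96 + 0.84 = 2.80:
- Carried forward: Φ(2.80 × 0.80 − 1.96) = Φ(0.28) = 61%.
- Same loss, only observed values used: Φ(2.80 × √0.80 − 1.96) = Φ(0.54) = 71%.

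Of the 19-point fall from 80%, about 9 points come from losing the participants and about 10 from carrying baseline forward.

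**3. Between arms.** Take two identical arms, each gaining 0.8 SD at end of treatment and holding 0.4 SD at the last visit. Expected spurious difference at the last visit, arm with less loss minus arm with more:
- Equal loss: 0.
- Loss during treatment, 5% against 25%: 0.95 × 0.4 − 0.75 × 0.4 = +0.08 SD, in favour of the better-retained arm.
- Loss after treatment, 5% against 25%: (0.95 × 0.4 + 0.05 × 0.8) − (0.75 × 0.4 + 0.25 × 0.8) = 0.42 − 0.50 = −0.08 SD, in favour of the arm with more loss.

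A simulation (41 per arm, four visits, correlation 0.5, random dropout, 4,000 runs) gave differences of about 0, +0.09 and −0.08 SD. The interaction test rejected in about 5%, 9.6% and 6% of runs, against the 5% set.

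If the true courses differ, equal loss is not harmless. An advantage of 0.5 SD at end of treatment that vanishes completely, with 25% lost afterwards in both arms, still shows as 0.25 × 0.5 = 0.125 SD (about 0.12 in simulation).

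**The case against.** The strongest reply is that no attrition rate is stated and that small losses do little harm: with 10% lost after treatment, 50% retention reads as 55%. That stands as a limit on size, not on direction. A further reply is that someone who stops exercising early may truly gain nothing, or may decline. Baseline carried forward would then be fair or even generous, while a missing-at-random model could be too optimistic. That also stands, so the dilution is stated as conditional.

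A reader might infer more than the article supports:

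- **That the rule decides the durability answer.** It does so only for participants seen at end of treatment and then lost. Its weight is their share.
- **That it biases the arm comparison, and in favour of the game.** The bias is about zero when loss and courses match, and its sign depends on when loss occurs. The remark about adherence in section 3 concerns training. It makes unequal loss during treatment plausible but says nothing about attendance at later follow-up.
- **That copied values make standard errors too small.** This does not hold for the comparison between arms, where each person contributes one score. In a simulation of 20,000 runs with 20% lost after treatment in both arms, the true SD of the difference was 0.226, the mean reported standard error 0.225 and the type I error 5.0%.
- **That the rule cuts power from 80% to 61%.** About half of that fall would occur under any method. Nor is 80% for 0.50 SD this trial's figure: with 41 per arm, Φ(0.5 × √(41/2) − 1.96) = Φ(0.30), about 62%.
- **That the article claims intention-to-treat requires this rule.** It pairs the two and does not argue that one requires the other.
- **That a missing sensitivity analysis is a fault.** A condensed article may leave that to the analysis plan.

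**Conclusion.** The concern holds in a bounded form. As the only stated method, carrying the last observation forward is poorly matched to the durability aim: it pulls the result toward a sustained effect in proportion to loss after treatment, whenever those lost would have declined. With half the gain truly kept, the overstatement is 5, 10 and 15 percentage points at 10%, 20% and 30% loss. If those lost would have gone on improving, the pull would run the other way.

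Loss during treatment dilutes the effect by the share lost if those participants would have gained, at a cost of about 10 points of power in the 20% example. The arm comparison is at risk only if loss or courses differ. In the example of unequal loss during treatment, the shift is under 0.1 SD and the interaction type I error is close to 10%. All sizes rest on assumed loss rates and courses.

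**What to change.** In section 2.8, replace the carry-forward sentence as the primary method. Fit a linear mixed model for repeated measures (REML, unstructured covariance, visit by arm) to all observed visits of all randomised participants, with baseline as one of the four visits. Take the sustained-effect contrasts, from end of treatment to each follow-up, from that model. State the missing-at-random assumption. Everyone with any measurement still contributes, so the intention-to-treat commitment is kept.

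The label mixed model ANOVA does not already deliver this. Section 2.7 ties it to "F-test (ANOVA repeated measure, within-between interactions) was chosen and inputted into the system", the classical form, which needs complete rows.

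The cost is about two sentences and slightly more analysis work in SPSS (MIXED procedure), with the sample size unchanged. The sustained-effect result may look less favourable. A sensitivity analysis that shifts missing follow-up values downward (delta adjustment) is a useful optional addition, since missing at random may itself be optimistic for those who leave.

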### Participants’ allocation

2.3

Selected stroke survivors will be randomized into either game-based circuit exercise (experimental group) or conventional circuit exercise (control group) using a stratified randomization method, with the use of sealed opaque envelopes by an independent researcher. Stratification variables are age, consisting of younger (40–59 years) and older adults (60–80 years), and disability level, namely 1 (no significant disability), 2 (slight disability) and 3 (moderate disability). Using the sealed envelope system, recruited participants will be stratified according to the sequence of age and disability level. Participants are then alternately allocated into each trial group according to their age and disability level categories. In this way, both the game-based circuit exercise and conventional circuit exercise trial group will consist of participants with comparable age and disability levels.

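### The time, group and time-by-group effects of the planned mixed ANOVA do not target the two aims; a baseline- and strata-adjusted contrast at a named visit would, with no new data and no change to the sample size.

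*Protocol article*

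**What the plan says.** Section 2.8 (Data analysis) fixes the method: "The effects of the interventions will be analyzed using mixed model ANOVA and reported as main time, group and time-group interaction effects", for every outcome and at one significance level. Section 2.7 (Sample size) repeats it: "This study will use mixed model analysis of variance (ANOVA) to analyze time, group and interaction effects of the interventions". It adds that the "F-test (ANOVA repeated measure, within-between interactions) was chosen and inputted into the system".

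Section 2.6 gives the assessment times: "The baseline and therapy outcomes at the end of week 12 of interventions and at a follow up at week 12 and 24" after the trial is completed. That makes four, counting baseline.

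Section 2.3 stratifies the allocation ("Stratification variables are age, consisting of younger" and older adults, plus disability level 1, 2 or 3), which gives six strata. Section 2.8 names no covariate, neither these factors nor the baseline value.

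The abstract and the end of the Introduction state two aims: to compare the effectiveness of the two circuits, and to learn whether the gains persist 12 and 24 weeks after the trial.

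**The concern.** If baseline is a level of time, the group main effect averages over a visit at which randomisation makes the expected difference zero. It therefore understates the benefit. The interaction asks only whether the two four-visit profiles are non-parallel. It names no visit and no direction, so a significant result could mean a lasting benefit, a benefit already lost, or one that appears late.

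The text names no visit or contrast as the treatment comparison. At stake is whether the named results can answer either aim, and whether precision available from the baseline value and the strata is left unused.

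**Working it through.** **Inputs.** From the article: 82 participants, 41 per arm, alpha 0.05 (section 2.7); four assessments (2.6); six strata (2.3). Not stated: effect size, within-person correlation ρ and number of measurements entered. Assumed: d = 0.5 SD, ρ from 0.3 to 0.8, compound symmetry, sphericity, no dropout.

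**1. The plan's own figure.** Section 2.7 reports that "a minimum sample of 82 subjects is required, that is, 41 participants in each trial group". The within-between interaction has λ = N·m·f²/(1−ρ) with df m−1 and (N−2)(m−1). With f = 0.13, m = 4 and ρ = 0.5, λ = 82 × 4 × 0.0169 / 0.5 = 11.09 on 3 and 240 df. Power is 80.0%, and 82 is the smallest balanced total. But f = 0.10 with m = 2 and ρ = 0.8, or f = 0.20 with m = 3 and ρ = 0, also gives 82. The figure is therefore not shown to be wrong, and it does not reveal how many measurements were entered.

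**2. Group main effect over four visits.**
- Constant benefit: (0 + d + d + d)/4 = 0.75d, or 0.375 SD at d = 0.5.
- Benefit at end of intervention only: d/4 = 0.25d.

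This step needs no assumed correlation.

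**3. What the interaction can distinguish.** Write v for the between-arm differences at the four visits, with mean v̄. Then λ = (n/2)·Σ(v − v̄)²/(1−ρ), with n = 41.
- Constant benefit: Σ = 0.375² + 3 × 0.125² = 0.1875.
- Benefit at end of intervention only: Σ = 0.375² + 3 × 0.125² = 0.1875.
- Benefit at the last follow-up only: the same value.

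At ρ = 0.5 all three give λ = 20.5 × 0.1875 / 0.5 = 7.69 and power 62.7%. The test responds identically to three different answers to the durability question.

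**4. Power at 41 per arm.** Group effect: λ = (n/2)·v̄²/[(1+3ρ)/4], df 1 and 80. Baseline-adjusted contrast at end of intervention: λ = (n/2)·d²/(1−ρ²), df 1 and 79. At ρ = 0.5 these are 20.5 × 0.1406 / 0.625 = 4.61 and 20.5 × 0.25 / 0.75 = 6.83.

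| Constant d = 0.5 | ρ 0.3 | ρ 0.5 | ρ 0.7 | ρ 0.8 |
|---|---|---|---|---|
| 3-df interaction | 47% | 63% | 86% | 97% |
| Group main effect | 68% | 56% | 48% | 44% |
| Baseline-adjusted, end of intervention | 65% | 73% | 88% | 96% |

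Fading benefit (d, d/2, 0) at ρ = 0.5: Σ = 0.1719, so the interaction has λ = 7.05 and power 58%. The group effect has 19% and the end-of-intervention contrast 73%. For the same profile the interaction has 44% at ρ = 0.3 (λ = 5.03) and 95% at ρ = 0.8 (λ = 17.62), against 65% and 96% for the contrast.

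If the effect is instead set so that the interaction has its planned 80% (ρ = 0.5, d = 0.60), the group effect has 72% and the end-of-intervention contrast 87%. Under an AR(1) correlation of 0.7 with constant d = 0.5, the figures are 62% for the interaction, 53% for the group effect and 88% for the contrast. The gap at high ρ thus depends on the correlation structure.

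**5. Validity and strata.** Simulated size under no effect, without stratum differences, is 5.5% for the group effect and 4.6% for the interaction (6,000 runs). With balanced strata omitted, the size of the group test falls to 3.9, 2.4 and 1.9% when strata explain 10, 20 and 30% of the variance (8,000 runs), so that test becomes conservative. Stable stratum differences cancel within person and leave the interaction unaffected. In the end-of-intervention contrast at ρ = 0.5, adding strata that explain a further 10 or 20% of residual variance raises λ to 6.83/0.9 = 7.59 or 6.83/0.8 = 8.54. Power rises from 73% to 78% or 82%.

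**The case against.** The strongest reply is that the trial was sized on the interaction, which does use baseline and serves as the treatment test, so the diluted group effect is only an accompanying output. That stands in part: the interaction is a valid test. It still cannot say when the arms differ or in which direction.

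A second reply is that repeated functional tests correlate highly; section 2.5 cites test-retest values of 0.89 to 0.99 for the three functional tests. Correlation over months will be lower, but at 0.7 to 0.8 under compound symmetry the power gain does almost disappear. The proposed contrast also has a blind spot: a benefit seen only at the last follow-up does not enter it. That is why the follow-up differences must be estimated as well.

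A reader might infer more than the article supports:
- *That the trial loses its planned power.* It does not: the 80% was set for the interaction itself.
- *That no between-arm estimate will be reported.* The article is silent on contrasts and intervals, and an unseen analysis plan may supply them.
- *That omitting the strata weakens every test.* It affects between-person comparisons. It does not affect the interaction unless strata change differently over time. An analysis plan could also add the factors.
- *That baseline is stated to be a time level.* It is inferred from the named effects and the sizing test.

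**Conclusion.** The point holds as one of targeting and efficiency, not validity. On the natural reading, the group effect is cut by a quarter for a constant benefit and by three quarters for one present only at end of intervention. The interaction does not separate a sustained from a vanished benefit. Those two results need no assumed correlation beyond a common one across visits.

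The power gain does depend on unstated quantities. For a constant 0.5 SD benefit under compound symmetry, the end-of-intervention contrast gains 18 points over the interaction at ρ = 0.3 (65 − 47) and 10 at ρ = 0.5 (73 − 63). It gains 2 at 0.7 (88 − 86) and loses 1 at 0.8 (96 − 97). The case for change therefore rests first on matching the analysis to the aims, and second on power. It is worth making before results are seen.

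**What to change.** Replace the effects named in sections 2.7 and 2.8 as the treatment analysis with:

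1. A repeated-measures model of the three post-baseline visits, with baseline value, age stratum, disability stratum, arm, visit and arm × visit.
2. The baseline-adjusted between-arm difference at end of intervention, with 95% CI, named as the treatment comparison.
3. For durability, the between-arm difference at each follow-up and the change from end of intervention to each follow-up (within and between arms), with 95% CIs. Persistence should not be inferred from a non-significant time effect.
4. The time × group interaction kept as supportive.

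The cost is wording. Every variable is already collected, the SPSS MIXED procedure fits the model, and the sample size stays at 82.
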